## 13.2 Sample Size

We anticipate enrolling a maximum of 760 patients (380 per arm). We anticipate an accrual rate of 180 patients per year (15 per month) based on similarly accruing studies of Alliance N1048 trial, NRG-GI002, and the OPRA trial. The total accrual period of this study is estimated to be 4.2 years, including start-up time.

For phase II portion, per study design, total of 296 evaluable patients (148 per arm) will be needed to evaluate the primary endpoint. Up to an additional 16 patients (5% inflation) might be accrued to account for cancellation after randomization and major violations. Thus, the total targeted accrual for phase II portion will be up to 312 patients.

## 13.3 Power Justification

The design of this trial is a randomized, seamless phase II/III trial. After a patient is registered, they will be assigned to one of the two treatment arms in a 1:1 ratio utilizing a dynamic allocation algorithm based on the methods by Pocock and Simon [46].

The patients included in the phase II endpoints analyses will be included in the phase III endpoints analyses. The accrual will not be halted while waiting for phase II endpoints to be matured and analyzed, unless we experience unexpected rapid accrual and/or unacceptably high treatment toxicity, or other unforeseen situations. If the criteria for continuation have been satisfied at conclusion of phase II portion, to protect the phase III comparison, the actual results of the phase II portion will not be released beyond the Alliance DSMB.

### 13.3.1 Phase II Portion:

The phase II portion of this trial is designed to primarily compare cCR rate in patients with locally advanced rectal cancer treated with LCRT, mFOLFIRINOX, followed by a selective WW approach (Arm A) versus those who are treated with LCRT, mFOLFOX6, followed by a selective WW approach (Arm B). The Phase II portion of this trial implements a group sequential design with a single interim analysis for futility evaluation, adopting Rho family ( $Rho=2$ ) beta spending function for controlling the overall type II error rate.

The OPRA trial reported 52.4% (87 out of 166 randomized to consolidation arm) of patients who achieved a sustained cCR and preserved the rectum. For the proposed trial, we assume a cCR rate of 50% in the control arm (Arm B). A total number of 296 evaluable patients will provide 90.5% power to detect an **17% increase** in cCR rate (67% in the experimental arm [Arm A]) at a one-sided type I error rate of 0.048. With the decision rules stated below in Section 6.4, this design provides the following design operation characteristics:

|                                                                                                           |                                                 |                                                 |
|-----------------------------------------------------------------------------------------------------------|-------------------------------------------------|-------------------------------------------------|
| If the true cCR rate is ...                                                                               | H1
Experimental arm: 67%
Control arm: 50% | H0
Experimental arm: 50%
Control arm: 50% |
| Then the probability of stopping at the interim analysis due to futility is ...                           | 0.024                                           | 0.560                                           |
| Then the probability of declaring that cCR rate of the experimental arm is superior to control arm is ... | 0.900                                           | 0.050                                           |

### 13.3.2 Phase III Portion:

The phase III portion of this trial is designed to primarily compare disease-free survival (DFS) in patients with locally advanced rectal cancer treated with LCRT, mFOLFIRINOX, followed by a selective WW approach (Arm A) versus those who are treated with LCRT, mFOLFOX6, followed by a selective WW approach (Arm B). Phase III portion implements a group sequential design with one futility interim analysis based on a non-binding beta spending function (Rho family with  $Rho=3.2$ ), which will be performed when 50% of DFS events have been observed (143 events). The OPRA trial reported a three-year DFS rate of 76% (95% CI, 69-83%) for patients who received chemoradiotherapy followed by consolidation chemotherapy (CRT-CNCT)[47]. A total number of 285 DFS events will provide 85% power to detect an effect size of hazard ratio (HR) = 0.70 (3-year DFS rate of 82.5% in the experimental arm A) at a one-sided type I error rate of 0.025. With further assumptions of an accrual rate of 180 patients per year and a minimum of four years of follow-up, a maximum of 760 patients (380 in each arm) are required to enroll, unless the study team makes a decision of early termination due to monitoring rules specified in section of 13.4.2 or 13.5.1.

With the decision rules stated below in Section 13.4.2, this design provides the following design operation characteristics for interim analyses:

|                                                            |                                                                                 |                                                   |                                                 |
|------------------------------------------------------------|---------------------------------------------------------------------------------|---------------------------------------------------|-------------------------------------------------|
| Analyses time point                                        | If the true 3-year DFS rate is ...                                              | H1
Experimental arm: 82.5%
Control arm: 76% | H0
Experimental arm: 76%
Control arm: 76% |
| interim analysis (futility only) at 50% of events observed | Then the probability of stopping at the interim analysis due to futility is ... | 0.016                                             | 0.500                                           |

## 13.4 Statistical Analysis Plan

### 13.4.1 Analysis Populations:

- **Intent-to-Treat (ITT) Population:** ITT population includes all patients who are properly randomized, regardless of the actual treatment received. The treatment grouping will be according to the original assignment at randomization.
- **Modified Intent-to-Treat (mITT) Population:** mITT population includes all patients who are properly randomized, completed LCRT and started at least one dose of protocol defined chemotherapy treatment. The treatment grouping will be according to the original assignment at randomization.
- **Per-Protocol (PP) Population:** PP population includes all patients who are deemed eligible after randomization, properly randomized, and received at least three cycles of chemotherapy after LCRT. The treatment grouping will be according to the actual treatment received during the first cycle of the chemotherapy.
- **Safety Population:** Safety population includes all patient who received any dose of treatment defined by protocol.

### 13.4.2 Primary Endpoint:

#### Phase II Portion:

Hypothesis testing analyses will be performed on mITT population. Sensitivity analyses will be performed on PP population.

- **Interim Analysis Decision Rule:** An interim analysis will be performed when 50% (74 in each arm) of patients are randomized and cCR status available. Difference of proportions test [33], [34] will be conducted to compare cCR rate in the experimental arm to cCR rate in the control arm. The estimated one-sided p-value will be compared to the following stopping boundaries:

| Testing: | One-sided P-value | Difference in proportions | Decisions                                                                                                                                                                                                            |
|----------|-------------------|---------------------------|----------------------------------------------------------------------------------------------------------------------------------------------------------------------------------------------------------------------|
| Futility | > 0.44            | < 0.012                   | Reject H1: concluding that the chance of cCR rate of the experimental arm being superior to the control arm is too low to continue the study. The accrual will be terminated if it does not reach target enrollment. |

If futility boundary is not crossed, then the trial will continue accrual and patient follow-up per protocol. The trial will not be halted while performing the interim analysis. However, if the accrual is especially rapid, we may temporarily suspend accrual to avoid missing important acute toxicity patterns and assigning patients to potentially ineffective treatment (futility of cCR rate endpoint in experimental arm).

- **Final Analysis Decision Rule:** If the trial continues after the interim analysis, the final cCR rate analysis will be performed when target accrual is reached and the cCR status are available on all treated patients. Difference of proportions test will be conducted to compare cCR rate in the experimental arm to cCR rate in the control arm. If the one-sided p-value of the comparison is < 0.05 (difference in proportion > 9.3%), then we will conclude the cCR rate in the experimental arm is superior to the control arm.

**Phase III Portion:**

The Phase III hypothesis testing analyses will be performed on ITT population. Sensitivity analyses will be performed on mITT and PP population. At interim and final analyses, stratified Cox model will be conducted to compare DFS in the experimental arm to DFS in the control arm with stratification factors as stratum, based on all data collected at the analysis time point.

- **Interim Analysis Decision Rule:** The interim analysis will be conducted when 50% of targeted events (about 143) which is estimated around 4.5 to 4.9 years after the first patient is randomized (about 3.6 to 8.4 months after all patients are enrolled). If the observed HR (stratified by stratification factors) at interim analysis is  $> 1.00$ , we will conclude that the chance of DFS in experimental arm being superior to that in control arm is too low. The results will be presented to Alliance DSMB and NCI for potential public release.
- **Final Analysis Decision Rule:** The final DFS analysis will be performed when at least 285 DFS events are observed combining the two arms. Stratified Cox model will be conducted to compare DFS in the experimental arm A to DFS in the control arm B. If the one-sided p-value of the comparison is  $< 0.025$ , then we will conclude the DFS in the experimental arm is superior to the control arm.

**13.4.3 Secondary Endpoints:**

The analyses of secondary endpoints will be conducted on mITT and PP population whenever it is applicable and plausible. Safety-related analyses will be performed on the safety population.

The distributions of time-to-event endpoints will be estimated, in each arm, using the method of Kaplan-Meier and compared by a stratified Cox regression model. The binary endpoints will be estimated, in each arm, and compared by chi-squared test or Fisher's exact test. Dose intensity and number of cycles will be summarized by mean, standard deviation, median, Q1, Q3, and range, in each arm, and compared by Wilcoxon Rank Sum test. The maximum grade for each type of adverse events that are possibly, probably, or definitely related to study treatments will be recorded for each patient. The frequency tables will be reviewed to determine the patterns. The overall adverse event rates for grade 3 or higher adverse events will be compared between two treatment groups using Chi-square test (or Fisher's exact test if the data in the contingency table is sparse).

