### 13.1.2 Secondary Endpoints:

- Organ-preservation-time (OPT): is defined as time from the date of randomization to the date of the first occurrence of the following events:
  - TME performed or attempted
  - Tumor that regrows after an initial apparent clinical and radiological CR
  - Death due to all causes
- Time to distant metastasis (TDM): is defined as time from the date of randomization to the date of first documented distant metastasis.
- Overall survival (OS): The OS is defined as time from the date of randomization to the date of death due to all causes.
- Adverse Events (AE) Rate: is defined as the proportion of patients experienced at least one Grade 3, Grade 4, or Grade 5 of each type of AE.

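### OS, organ-preservation time, time to distant metastasis and phase II cCR have no intention-to-treat analysis: all are analysed only in populations defined by events after randomization

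*Combined protocol and SAP*

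**What the plan says.** Section 13.4.1 defines four populations. ITT is everyone properly randomized, as assigned. mITT keeps the assigned grouping but requires that patients "completed LCRT and started at least one dose of protocol defined chemotherapy treatment". PP requires confirmed eligibility and at least three chemotherapy cycles, and groups patients by the treatment received in the first cycle.

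These populations are then assigned as follows:

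- **Phase II cCR (13.4.2):** "Hypothesis testing analyses will be performed on mITT population", with sensitivity analyses on PP only. The test is unstratified: "Difference of proportions test will be conducted to compare cCR rate in the experimental arm to cCR rate in the control arm".
- **Phase III DFS (13.4.2):** ITT, by a Cox model stratified on the allocation factors, with mITT and PP as sensitivity analyses.
- **Secondary endpoints (13.4.3):** "The analyses of secondary endpoints will be conducted on mITT and PP population whenever it is applicable and plausible". Safety analyses use the safety population.

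Section 13.1.2 starts the clock at randomization for all three time-to-event secondary endpoints. For example: "The OS is defined as time from the date of randomization to the date of death due to all causes". Section 12.5 already requires relapse, progression and survival data on registered patients who never start treatment. Section 4.5 allocates by Pocock-Simon minimization on T stage, N stage and distance from the anal verge.

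**The concern.** The arm is assigned at registration, before LCRT, and no blinding is described. The study calendar places the pre-chemotherapy visit at about week 10. A patient who dies, progresses or withdraws before the first chemotherapy dose is in the ITT set for DFS but not in mITT or PP. A death during LCRT would therefore be a DFS event and would not appear in the OS analysis, so the two results would describe different patients.

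For cCR, the decision to start chemotherapy is taken knowing whether the doublet or the triplet comes next. If more poor responders fall out before that point in one arm, the mITT rate in that arm is raised. The phase II result bears on whether phase III continues (Section 13.3). The early-off-treatment monitoring in Section 13.5.1 would not reveal the problem, because its denominator also starts at the first chemotherapy dose. PP is more exposed still, since reaching three cycles depends on tolerating the assigned regimen.

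**Working it through.** **1. The plan's own design.** Inputs from 13.3.1 and 13.4.2: 148 per arm, cCR 50% v 67%, futility stop if one-sided p > 0.44 at half the information, final test at p < 0.05. A two-look normal calculation gives type I error 0.0480, power 90.6%, and futility stopping probabilities of 0.560 under H0 and 0.024 under H1. The plan states 0.048, 90.5%, 0.560 and 0.024. The design reproduces, so the issue is the population, not the arithmetic.

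**2. Which denominator the figures imply.** The critical difference is 1.645 × √(2 × 0.25/n).

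- n = 156 per arm: 1.645 × √(0.5/156) = 0.0931, the stated 9.3%.
- n = 148 per arm: 1.645 × √(0.5/148) = 0.0956, or 9.6%.

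The stated threshold thus corresponds to all 312 patients with none excluded. Regrowth Rule #1 in 13.5.1 likewise multiplies 156 by 0.593. The 50% control rate is drawn from 87/166 = 52.4% of patients randomized to the earlier trial's consolidation arm. Both figures fit ITT better than mITT.

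**3. Effect of exclusions on the cCR test.** Assumptions, none from the documents: true all-randomized cCR is 50% in both arms, every excluded patient is a non-cCR, 156 are randomized per arm, and the test is a single look at one-sided 0.05. With loss e in an arm, its mITT rate is 0.5/(1 − e) on 156(1 − e) patients.

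| Loss, control / experimental | mITT rates | Spurious difference | One-sided error |
|---|---|---|---|
| 5% / 5% | 52.6% / 52.6% | 0.0 points | 0.050 |
| 4% / 6% | 52.1% / 53.2% | 1.1 points | 0.073 |
| 3% / 7% | 51.5% / 53.8% | 2.2 points | 0.103 |
| 5% / 10% | 52.6% / 55.6% | 2.9 points | 0.126 |

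Worked case, 4%/6%: n = 149.8 and 146.6, pooled rate 0.526, SE = √(0.526 × 0.474 × (1/149.8 + 1/146.6)) = 0.0580. The critical difference is 1.645 × 0.0580 = 0.0954, z = (0.0954 − 0.0111)/0.0580 = 1.45, and the upper tail is 0.073.

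The no-cCR assumption matters. Section 1.4 cites an 18% pCR rate after LCRT alone. Using that as a stand-in for cCR among the excluded, 3%/7% gives (0.5 − 0.03 × 0.18)/0.97 = 0.510 and (0.5 − 0.07 × 0.18)/0.93 = 0.524. The difference is 1.4 points; z = (0.0955 − 0.0142)/0.0581 = 1.40, and the error is about 0.08.

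**4. Power if cCR is analysed by ITT.** All 312 patients, unassessed counted as not cCR, one-sided 0.05, single look:

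- If 50% and 67% are already all-randomized rates: 92.3%.
- If they are mITT rates with equal loss in both arms: 90.5% (3% lost), 89.3% (5%), 87.3% (8%), 85.9% (10%). At 5% the rates are 0.95 × 50% = 47.5% and 0.95 × 67% = 63.65%.

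The futility look takes off a little more; in simulation of the planned design it cost 0.7 points (0.913 to 0.906).

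**5. Omitting the allocation factors.** Simulation of 4,000 trials per setting: N = 296, minimization with a 0.8 biased coin, assumed factor prevalences and effects, treatment log odds ratio 0.71 (50% to 67%), compared with a Cochran-Mantel-Haenszel (CMH) test.

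| Prognostic effect | Error, unstratified / CMH | Power, unstratified / CMH |
|---|---|---|
| None | 0.043 / 0.046 | 0.913 / 0.905 |
| Moderate | 0.040 / 0.049 | 0.892 / 0.896 |
| Strong | 0.035 / 0.050 | 0.835 / 0.861 |

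The unstratified test errs on the conservative side. Stratifying changes power by about −1 to +3 points.

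**The case against.** Several counter-arguments are sound and limit the point.

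- **mITT is a deliberate phase II choice.** The portion is sized on evaluable patients with 5% inflation, and cCR is defined at the end of TNT over the analysis population. LCRT is the same in both arms, and mITT keeps the assigned grouping, so differential loss is possible but not built in. This stands: it makes the bias conditional. It does not explain the absence of even a sensitivity ITT analysis.
- **Toxicity stops.** A reader might infer that early stops for triplet toxicity vanish from mITT. They do not: one dose of chemotherapy keeps a patient in. Only PP drops stops before three cycles, and for cCR it is a sensitivity set.
- **Size.** A reader might take 5% loss in the triplet arm alone, turning 67% into 63.7%, as a 3.3-point bias. That assumes no loss in control and no cCR among those lost, and sets a one-arm change against a between-arm threshold. With 5% loss in each arm the difference moves from 17.0 to 16.15 points, and the error is unchanged.
- **Stratification.** A reader might infer that ignoring the allocation factors biases the cCR test. It does not; it makes the test conservative. Part of the shortfall appears even with no prognostic effect (0.043), so not all of it comes from the omitted factors.
- **Consequences.** If the trial continues, phase II results stay with the DSMB, and the decisive DFS test is already ITT and stratified. That limits the harm for cCR. It does not answer the gap for OS, OPT and TDM.

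**Conclusion.** The point holds as a gap in the analysis populations. No section provides an ITT analysis of OS, OPT, TDM or cCR, although the three time-to-event endpoints run from randomization and DFS is analysed on ITT. The wording about applicability in 13.4.3 qualifies the use of mITT and PP; it does not bring in ITT.

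For cCR, bias requires differential loss before the first chemotherapy dose. Under the stated assumptions the one-sided error is 0.050 with equal loss, about 0.07 at 4%/6% and about 0.10 at 3%/7%, and lower if some excluded patients would have reached cCR. The loss rates are illustrative.

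For OS no size can be given, because the documents contain no rate of death or failure before chemotherapy. A claim that the OS result would be driven by this selection is not supported. Phase III DFS is not affected. The missing stratification is a minor efficiency matter, separate from bias.

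**What to change.** 1. In 13.4.3, make ITT the primary population for OS, OPT and TDM, with mITT and PP as sensitivity analyses.
2. In 13.4.2, add an ITT analysis of phase II cCR with unassessed patients counted as not cCR, preferably as the primary test. Report the number of exclusions and the reasons by arm.
3. State the critical difference for the number actually analysed (9.3 points at 156 per arm, 9.6 at 148). Apply the futility rule (p > 0.44) and the final rule (p < 0.05) on the p-value scale. Restate the interim trigger so that patients who never reach assessment are counted.
4. Separately, and as an efficiency measure only, test cCR by CMH stratified on T stage, N stage and distance, with a prespecified rule for collapsing sparse strata. Eligibility restricts N0 disease, so some of the 12 cells will be small.

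**Cost.** No extra patients, and no new survival data, since 12.5 already requires follow-up of never-treated patients. Imaging after an early stop is left to the treating team (12.3.1), so OPT and TDM dates may be less regular for these patients; the ITT analysis of DFS already carries that limitation. ITT power for cCR is about 0.89 with 5% loss per arm, and higher if the assumed rates are already all-randomized rates. The thresholds and interim trigger must be restated, so this is a little more than a wording change.

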### **2.2 Secondary objective(s)**

**2.2.1** To evaluate and compare organ-preservation-time (OPT) between two treatment arms.

**2.2.2** To evaluate and compare time to distant metastasis between two treatment arms.

**2.2.3** To evaluate and compare overall survival (OS) between two treatment arms.

**2.2.4** To evaluate and compare toxicity profiles of TNT between two treatment arms.

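### Time to distant metastasis is to be estimated by Kaplan-Meier although death without metastasis is a competing event; cumulative incidence should be used instead

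*Combined protocol and SAP*

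**What the plan says.** Section 13.1.2 states that TDM "is defined as time from the date of randomization to the date of first documented distant metastasis". Death does not appear in that definition. The other time-to-event endpoints differ: organ-preservation-time in the same section lists "Death due to all causes" as an event, DFS in Section 13.1.1 also includes all-cause death, and overall survival is death itself.

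TDM is a named between-arm objective. Objective 2.2.2 reads "To evaluate and compare time to distant metastasis between two treatment arms".

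Section 13.4.3 covers all secondary time-to-event endpoints together: "The distributions of time-to-event endpoints will be estimated, in each arm, using the method of Kaplan-Meier", and they are to be "compared by a stratified Cox regression model". It makes no exception for TDM. Section 13 mentions neither competing risks nor cumulative incidence, and gives no rule for a patient who dies without metastasis.

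**The concern.** For DFS, organ-preservation-time and overall survival, death is an event and Kaplan-Meier estimates a real probability. For TDM it does not. A patient who dies without metastasis can never develop one, yet the Kaplan-Meier calculation removes that patient from the risk set as if lost to follow-up, and gives the removed patient the same future metastasis risk as those still observed. The complement of the curve therefore estimates metastasis risk in a hypothetical population in which nobody dies of anything else. It exceeds the actual proportion of patients who develop metastasis whenever some die without it.

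The metastasis percentages per arm are at stake. The arms differ in chemotherapy intensity, and Section 13.5.1 monitors grade 4 or higher related non-hematologic events in each arm separately, so unequal treatment-related mortality cannot be ruled out in advance. If deaths without metastasis are unequal, the overstatement is unequal too.

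**Working it through.** **Is there a figure to reproduce?** No. The documents give no rate, event count or power for TDM, and no rate of death without metastasis. The check therefore concerns the direction of the bias and its plausible range.

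**Formulas.** With constant cause-specific hazards h1 (distant metastasis) and h2 (death without metastasis), at time t:

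- 1-KM = 1 − exp(−h1·t)
- Cumulative incidence of metastasis (CIF) = h1/(h1+h2) × [1 − exp(−(h1+h2)·t)]
- Deaths without metastasis = h2/(h1+h2) × [1 − exp(−(h1+h2)·t)]

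For any h2 > 0 and t > 0, 1-KM is larger than CIF.

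**Assumed hazards, 5 years.** The hazards are assumptions. Worked example for 0.06 and 0.02 per year: 1-KM = 1 − exp(−0.30) = 25.9%; CIF = 0.75 × [1 − exp(−0.40)] = 24.7%; deaths = 0.25 × [1 − exp(−0.40)] = 8.2%.

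| h1 | h2 | 1-KM | CIF | Deaths without metastasis | Excess (points) |
|---|---|---|---|---|---|
| 0.05 | 0.01 | 22.1% | 21.6% | 4.3% | 0.5 |
| 0.06 | 0.015 | 25.9% | 25.0% | 6.3% | 0.9 |
| 0.06 | 0.02 | 25.9% | 24.7% | 8.2% | 1.2 |
| 0.06 | 0.03 | 25.9% | 24.2% | 12.1% | 1.8 |
| 0.07 | 0.03 | 29.5% | 27.5% | 11.8% | 2.0 |

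**Calibration to the plan's DFS assumptions.** Section 13.3.2 assumes 3-year DFS of 76% in the control arm and a "3-year DFS rate of 82.5% in the experimental arm A". If DFS is exponential, the total hazards are −ln(0.76)/3 = 0.0915 and −ln(0.825)/3 = 0.0641 per year. Set h1+h2 equal to this total and vary the share h2/(h1+h2). Local DFS events are ignored, which puts the metastasis percentages on the high side. Control arm at 5 years:

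| Share of first events that are deaths without metastasis (assumed) | 1-KM | CIF | Excess (points) |
|---|---|---|---|
| 5% | 35.2% | 34.9% | 0.4 |
| 10% | 33.7% | 33.0% | 0.7 |
| 20% | 30.6% | 29.4% | 1.3 |
| 30% | 27.4% | 25.7% | 1.7 |
| 40% | 24.0% | 22.0% | 2.0 |

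Excesses are taken from unrounded values. Over the same shares, the control-arm excess at 3 years is 0.1 to 0.8 points, and the experimental-arm excess at 5 years is 0.2 to 1.0 points.

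**Unequal deaths.** Give both arms the same metastasis hazard, 0.8 × 0.0915 = 0.0732 per year, with assumed death hazards of 0.01 and 0.03 per year. At 5 years 1-KM is 30.6% in both arms. The cumulative incidences are 29.9% and 28.6%, so the overstatement is 0.7 points in one arm and 2.1 in the other.

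**The case against.** Four points can be made for the plan.

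1. **The text never says that deaths are censored.** This is true; it is an inference. But Kaplan-Meier has no other treatment for a death that is not an event, so applying the plan as written leads there.

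2. **The planned comparison is sound.** This stands in full. A stratified Cox model that censors at death estimates a cause-specific hazard ratio, and the overstatement does not touch it. The point concerns only the estimated curves and the percentages read from them.

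3. **No metastasis rate is promised.** The plan speaks of distributions and sets no landmark percentage or decision threshold for TDM, so harm arises only if the curve is read as absolute risk. This is also correct. Even so, a curve estimated per arm for a named objective invites that reading, and a curve labelled as cause-specific, with no incidence claim, would answer less of the clinical question than cumulative incidence does.

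4. **The bias is small next to sampling error.** With 380 patients per arm and 25% incidence, the binomial standard error is √(0.25 × 0.75/380) = 2.2 points, before any loss from censoring or from the smaller analysis sets. An excess of 0.5 to 1.2 points is about a quarter to a half of that. This supports the low grading. It does not favour keeping an estimator with a known direction of error when the correct one needs no extra data.

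**Conclusion.** The concern holds. For TDM, the plan names an estimator that overstates the incidence of metastasis whenever some patients die without it, and nothing in Section 13 corrects this.

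At 5 years the overstatement is about 0.5 to 1.2 points if 4-8% of patients die without metastasis, and about 2 points if 12% do. These figures rest on constant hazards and on assumed death rates that the documents do not supply; calibration to the plan's own DFS rates gives the same order of size.

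The stratified Cox comparison for TDM, and the analyses of cCR, DFS, organ-preservation-time and overall survival, are unaffected. Sample size and decision rules do not change. It is a minor improvement to a secondary endpoint.

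**What to change.** In Section 13.4.3, exempt TDM from the Kaplan-Meier rule. State that TDM will be summarised in each arm by the cumulative incidence function (Aalen-Johansen estimator), with death without distant metastasis as a competing event, and that patients alive without metastasis are censored under a stated rule. Keep the stratified Cox model and label its result a cause-specific hazard ratio. A Gray test or Fine-Gray model may be added as a supplement but is not needed.

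Redefining the endpoint as distant-metastasis-free survival, with death as an event, would make Kaplan-Meier appropriate, but it changes the endpoint and Objective 2.2.2, so it is the less attractive route.

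The cost is a few lines of SAP text. Standard software does the estimation, and dates of death are already needed for overall survival. The change is best made before TDM results by arm are seen, so that the estimator is not chosen after the fact.
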